## Abstract

**Background:**

This paper describes Project FIT, a collaboration between the public school system, local health systems, physicians, neighborhood associations, businesses, faith-based leaders, community agencies and university researchers to develop a multi-faceted approach to promote physical activity and healthy eating toward the general goal of preventing and reducing childhood obesity among children in Grand Rapids, MI, USA.

**Methods/design:**

There are four overall components to Project FIT: school, community, social marketing, and school staff wellness - all that focus on: 1) increasing access to safe and affordable physical activity and nutrition education opportunities in the schools and surrounding neighborhoods; 2) improving the affordability and availability of nutritious food in the neighborhoods surrounding the schools; 3) improving the knowledge, self-efficacy, attitudes and behaviors regarding nutrition and physical activity among school staff, parents and students; 4) impacting the 'culture' of the schools and neighborhoods to incorporate healthful values; and 5) encouraging dialogue among all community partners to leverage existing programs and introduce new ones.

**Discussion:**

At baseline, there was generally low physical activity (70% do not meet recommendation of 60 minutes per day), excessive screen time (75% do not meet recommendation of < 2 hours per day), and low intake of vegetables and whole grains and high intake of sugar-sweetened beverages, French fries and chips and desserts as well as a high prevalence of overweight and obesity (48.5% including 6% with severe obesity) among low income, primarily Hispanic and African American 3^rd^-5^th ^grade children (n = 403).

**Trial registration:**

ClinicalTrials.gov NCT01385046

## Background

Poor nutrition, physical inactivity and obesity are considered the most pressing health issues in pediatrics and child health. About 75% of U.S. students do not consume 5 or more fruits and vegetables per day [1] and about 60% of children ages 6-11 years do not obtain the recommended 60 min per day of physical activity [2]. While obesity rates have increased across all segments of the population, they have increased most drastically (and are the highest point estimates) among low-income and Hispanic and Black children [3]. Thus, there is an important need to focus intervention on these groups of children [4]; however, few intervention studies have focused on low-income and/or minority children [5-10].

In an effort to improve key behaviors, knowledge, self-efficacy, and attitudes regarding physical activity and nutrition, we developed and will implement an intervention targeted at schools and neighborhoods with predominantly Hispanic and/or Black low-income students (95% of students qualifying for free and reduced lunch). This paper presents an overview of Project FIT, a community- and school-based intervention. The study design, implementation, and preliminary baseline results are explained within this paper.

## Methods/Design

### What Is Project Fit?

The overall objective of Project FIT was to increase physical activity and improve healthy eating among the school children of four urban, low-income elementary schools in Grand Rapids, MI. The project aimed to accomplish this objective by: 1) increasing access to safe and affordable physical activity and nutrition education opportunities in the schools and in the surrounding neighborhoods; 2) improving the affordability and availability of nutritious food in the neighborhoods surrounding the schools; 3) improving the knowledge, self-efficacy, attitudes and behaviors regarding physical activity and nutrition among school staff, parents and students; 4) impacting the 'culture' of the schools and neighborhoods to incorporate healthful values; and 5) encouraging dialogue among community partners to leverage existing programs and introduce new ones. The overall project is comprised of four components including: school, community, social marketing, and school staff wellness.

Project FIT built upon the many strengths and assets that currently exist within the Grand Rapids Public School District and the Grand Rapids community including (but not limited to): innovative school nutrition services, comprehensive school nursing programs, solid academic programming, and strong existing partnerships between the school system and community-based organizations. In addition, an advisory board was established and will meet quarterly throughout the project. A list of the advisory committee members and project partners is provided in Table 1.

**Table 1 T1:** Project FIT Advisory Committee Members and Project Partners.

### Theoretical Framework

Project FIT is guided by the social-ecological model [11] as a theoretical framework and social marketing principles [12] as a strategic tool. The social ecological model underscores the importance of multiple levels of influence on individual behavior. Additionally, components of the social cognitive theory [12] were implemented to promote the children's attitudes and self-efficacy for making desirable physical activity and nutrition choices. Social marketing refers to the use of (commercial) marketing techniques to design, manage, and implement programs to promote socially beneficial changes in behavior [12,13]. With a particular focus on branding and promotion, various promotional activities were combined with physical activity and nutrition programs to remind and motivate participants to engage in the promoted behaviors. The project was branded as Project FIT, a program that cultivates and reinforces individuals' physical activity and healthy eating.

### Setting And Participants

General characteristics of the schools and participants are shown in Table 2. Five elementary schools located in the Grand Rapids school district were selected by the superintendent to be part of the study (four intervention and 1 control). All schools reported greater than 95% of students qualifying for the Free or Reduced Lunch Program. Child-specific assessments were made on students in grades 3-5. A total of 434 third to fifth grade children were enrolled in the study out of 768 possible (57% overall participation rate; 54% in the intervention schools and 67% in the control school). Third and fourth graders at each school will be followed over the two-year period (Fall 2009 - Spring 2011) to determine the project's impact. The primary parental language (e.g., spoken at home) for the intervention and control schools was as follows: English, 37.6% and 48.6%; Spanish, 19.0% and 38.5%; Other, 1.0% and 0%; did not report, 41.5% and 12.8%, respectively. To have sufficient power to detect a difference of 1000 steps/day (standard deviation 2500 steps/day) or 2 fruit and vegetable servings per week (standard deviation 5 servings per week) or 5 hours of screen time per week (standard deviation 12 hours per week) between intervention and control group with power 0.80 and alpha 0.05, a minimum of 200 subjects were needed. Parental consent and child assent were obtained prior to data collection. All aspects of the study protocol were approved by the Grand Rapids Public School District's and Michigan State University's Institutional Review Boards. Students who returned their completed forms were given a $10 gift card for their families regardless of whether they decided to participate in the study. Parent survey and focus group participants were asked to sign a written consent form prior to participation. For the community component, the target communities were defined as the attendance areas of the four intervention schools plus 400 meters (approximately 0.25 miles).

**Table 2 T2:** Demographic characteristics of the schools and study population, Fall 2009.

	Control	Intervention				Total
		A	B	C	D	
School Enrollment (PK-5)	435	456	235	462	362	1950
Total Eligible Sample (3-5)	170	174	87	181	156	768
Sample Size	114	85	60	86	89	434
% Response	67%	49%	69%	48%	57%	57%
% Free-Reduced Lunch	98.0%	95.3%	97.8%	96.5%	96.7%	96.9%

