***Screen Time***							
Weekday TV (hrs/d)	1.4 (1.4)	1.7 (1.5)	1.6 (1.4)	1.9 (1.5)	1.8 (1.4)	1.8 (1.5)	1.7 (1.5)
Weekend TV (hrs/d)	2.2 (1.3)	2.4 (1.3)	2.3 (1.3)	2.4 (1.4)	2.4 (1.4)	2.4 (1.4)	2.4 (1.4)
Weekly TV (hrs/d)	1.7 (1.2)	1.9 (1.3)	1.8 (1.3)	2.0 (1.4)	2.0 (1.3)	2.0 (1.3)	1.9 (1.3)
Weekday Screen Time (hrs/d)	3.7 (3.0)	3.4 (3.0)	3.5 (3.0)	5.1 (3.4)	3.9 (3.4)	4.4 (3.4)	4.1 (3.3)
Weekend Screen Time (hrs/d)	5.6 (3.1)	4.7 (3.0)	5.1 (3.1)	6.0 (3.0)	4.9(3.1)	5.4 (3.1)	5.3 (3.1)
Total Screen Time (hrs/d)	4.3 (2.8)	3.8 (2.8)	4.0 (2.8)	5.4 (3.2)	4.2 (3.2)	4.7 (3.2)	4.5 (3.1)
% ≥ 2 hrs/d screen time	74.4%	73.1%	73.7%	82.1%	71.8%	76.7%	75.6%

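### The screen-time power statement assumes an SD of 12 h/week, but the article's own baseline table implies about 21.7 h/week, so 200 children do not give power 0.80 for that outcome

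*Protocol article*

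**What the plan says.** The protocol article, under Setting And Participants, justifies the sample size with three alternative scenarios in one sentence. Two are "a difference of 1000 steps/day (standard deviation 2500 steps/day) or 2 fruit and vegetable servings per week (standard deviation 5 servings per week"). The third is "5 hours of screen time per week (standard deviation 12 hours per week) between intervention and control group with power 0.80 and alpha 0.05". For all three it concludes that "a minimum of 200 subjects were needed". It does not state the sidedness of the test, the split between groups, or whether the SDs refer to a single occasion, a change or a baseline-adjusted value.

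The Screen time paragraph under School Level defines the outcome as weekly self-reported television, video games and online computer use. Table 3 reports the baseline for that sum as "Total Screen Time (hrs/d) 4.3 (2.8) 3.8 (2.8) 4.0 (2.8) 5.4 (3.2) 4.2 (3.2) 4.7 (3.2) 4.5 (3.1"). The columns are control males, females and total, then intervention males, females and total, then the whole sample. The table footnote says that bracketed values are standard deviations.

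**The concern.** The planning SD and the observed SD describe the same variable, once both are in hours per week, and the planning value is just over half the observed one (12/21.7 = 0.55). Required sample size grows with the square of the SD, so this is a large gap. The article prints both figures and does not comment on the difference.

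Screen time is one of only three outcomes used to justify the sample size. A reader who accepts the sentence as it stands could take a null screen-time result as a well-powered negative, when an unadjusted comparison would miss a true 5 h/week difference nearly half the time or more.

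**Working it through.** **Inputs.** Difference 5 h/week, SD 12 h/week, power 0.80, alpha 0.05 and 200 children (Setting And Participants). Observed SD 3.1 h/d overall, 2.8 control, 3.2 intervention (Table 3). Numbers 106 v 297 (Table 3) and 114 v 320 enrolled (Table 2: 434 − 114 = 320). Assumed: two-sided test, independent children.

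**Reproducing the stated 200.** Per-arm n = 2(1.960 + 0.842)²/d², that is 15.70/d².
- Steps: d = 1000/2500 = 0.40. Fruit and vegetables: d = 2/5 = 0.40. n = 15.70/0.16 = 98.1, so 99 per arm, 198 in total. This matches 200.
- Screen time at SD 12: d = 5/12 = 0.417. n = 15.70/0.1736 = 90.4, so 91 per arm, 182 in total. At 100 per arm power is 0.84 (0.83 with the noncentral t).

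The 200 is therefore reproduced with a two-sided test and an equal split, and screen time is not the scenario that sets it. A one-sided test (156 and 144) or a 4:1 split (310 and 285) does not give 200.

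**Is the Table 3 row the right comparator?** It is an average over the week: control (5 × 3.5 + 2 × 5.1)/7 = 3.96, printed 4.0; intervention (5 × 4.4 + 2 × 5.4)/7 = 4.69, printed 4.7. Weekly hours are exactly 7 times this row, so the SDs are:
- overall 7 × 3.1 = 21.7 h/week
- control 7 × 2.8 = 19.6 h/week
- intervention 7 × 3.2 = 22.4 h/week

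The pooled within-group SD, √[(105 × 2.8² + 296 × 3.2²)/401] = 3.10 h/d, gives the same 21.7.

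**Power for 5 h/week at SD 21.7.** d = 5/21.7 = 0.230. Power ≈ Φ(5/SE − 1.960), with SE = 21.7 × √(1/n₁ + 1/n₂).

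| Numbers | SE (h/week) | Power |
|---|---|---|
| 100 v 100 (stated minimum, equal split) | 3.07 | 0.37 |
| 106 v 297 (Table 3) | 2.46 | 0.53 |
| 114 v 320 (enrolled) | 2.37 | 0.56 |

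The noncentral t gives 0.368 and 0.529 for the first two rows.

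Sensitivity:
- Rounding of 3.1 (3.05 to 3.15) moves the first row between 0.38 and 0.36.
- SDs of 19.6 to 22.4 move it between 0.44 and 0.35.
- Arm-specific SDs at 106 v 297 give 0.58.
- Only third and fourth graders are followed over the two years. Counts by grade are not given. If they are two thirds of the children (an assumption), power is about 0.38 from the Table 3 numbers and about 0.40 from the enrolled numbers.

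**Sample size and detectable difference at SD 21.7.** Power 0.80 for 5 h/week needs 15.70/0.0531 = 296 per arm, 592 in total at an equal split. The difference detectable with power 0.80 is 2.802 × SE: 8.6 h/week at 100 v 100, 6.9 at 106 v 297 and 6.6 at 114 v 320.

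**Could 12 be a baseline-adjusted SD?** Adjusted SD = 21.7 × √(1 − r²). Setting this to 12 gives r = √(1 − (12/21.7)²) = 0.83. For a change score, 21.7 × √(2(1 − r)) = 12 gives r = 0.85. At r = 0.5 the adjusted SD is 18.8 and power is 0.47 (100 v 100) or 0.65 (106 v 297). At r = 0.7 it is 15.5 and power is 0.63 or 0.81.

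**The case against.** The strongest reply is that a planning SD is a prior assumption, possibly fixed before any baseline data existed, and that a later, larger SD makes it optimistic rather than miscalculated. That stands. A reader might infer an arithmetic error in the 200, but the figure reproduces from its inputs.

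A second tempting inference is that the trial's power for screen time is 0.37. That figure belongs only to the stated minimum split equally. The trial enrolled 434, and at the actual numbers power is 0.53 to 0.56: higher, but still well short of 0.80.

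Third, the article does not say what kind of SD the 12 is, and the study has repeated measures. This weakens the contradiction without removing it. The sentence describes a difference between groups and gives no correlation, and reconciling the figures would take a pre-post correlation of about 0.83 on children's self-report. In fairness, baseline adjustment with r near 0.7 would bring power to about 0.81 at the Table 3 numbers, but not at 200 children, and still before clustering.

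Television alone has an SD of 1.3 h/d, or 9.1 h/week, which would fit under 12. It is not the outcome as the article defines it.

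Finally, a reader might conclude that the whole sample-size justification fails, or that screen time ought to be demoted to a secondary outcome. Neither follows. The steps and fruit-and-vegetable scenarios set the 200 and are untouched by this point, and the article names no primary outcome from which to demote anything.

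**Conclusion.** The point holds as an unsupported planning assumption that the article's own baseline data contradict. The statement that 200 children give power 0.80 for 5 h/week of screen time is not sustained. At the observed SD, power is about 0.37 at that minimum, 0.53 at the Table 3 numbers and 0.56 at enrolment.

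These figures rest on a two-sided alpha of 0.05, an unadjusted comparison, the baseline SD carrying over to follow-up, and independent children. The last assumption is favourable to the trial: with five schools, one of them the only control, any positive within-school correlation lowers power further. Nothing here bears on the steps or fruit-and-vegetable scenarios.

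**What to change.** Rewrite the screen-time part of the sample-size sentence:
- Use the observed SD of 21.7 h/week (control 19.6, intervention 22.4), and say that it comes from the Fall 2009 baseline.
- Give either the achieved power for 5 h/week or the difference detectable with power 0.80 (8.6 h/week at 100 v 100, about 6.6 to 6.9 at the enrolled or Table 3 numbers). Say that these ignore clustering and are therefore optimistic.
- Drop the claim that 200 children suffice for this outcome.
- If 12 h/week was meant as a change or adjusted SD, say so and state the correlation assumed.

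Analyse screen time adjusted for each child's Fall 2009 value. This recovers precision. It also deals with a baseline gap between groups of 4.7 − 4.0 = 0.7 h/d, or 4.9 h/week, which is about the size of the target difference.

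The cost is one restated sentence and a covariate already collected. The stated power becomes less favourable; recruitment and measurement do not change.

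### The stated minimum of 200 children gives power 0.80 only with equal arms; at the enrolled split of 114 v 320 it gives about 0.70 (0.73 for screen time)

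*Protocol article*

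**What the plan says.** The Protocol article gives its only power statement under Setting And Participants. The target differences are "a difference of 1000 steps/day (standard deviation 2500 steps/day"), "2 fruit and vegetable servings per week (standard deviation 5 servings per week") and "5 hours of screen time per week (standard deviation 12 hours per week"), to be detected "between intervention and control group with power 0.80 and alpha 0.05". The conclusion is that "a minimum of 200 subjects were needed". The statement gives no allocation ratio and does not say whether the test is one- or two-sided.

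The same section describes the five schools as "four intervention and 1 control". Table 2 lists 114 enrolled children in the control school and 85, 60, 86 and 89 in the four intervention schools. Participation was "54% in the intervention schools and 67% in the control school". Enrolment covers grades 3 to 5, but for the two-year impact comparison the section says "Third and fourth graders at each school will be followed over the two-year period".

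**The concern.** A total sample size has a definite power only once the split between the arms is fixed. For a given total, power is highest with equal arms and falls as they become unequal. Here the design is unequal by construction, four schools to one, and the enrolled children are split about 1:2.8. If 200 was worked out for equal arms, it does not deliver the stated 0.80 in this study.

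This matters because 200 is the only sufficiency threshold in the document and it is given as a single total. A total hides the fact that the control school is the limiting arm. Anyone who later checks the number of children with two-year data against 200 would be using a threshold that is too low for this allocation.

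**Working it through.** **Inputs.** All come from Setting And Participants and Table 2.
- Standardised differences: steps 1000/2500 = 0.40; fruit and vegetables 2/5 = 0.40; screen time 5/12 = 0.417.
- Alpha 0.05, taken as two-sided; power 0.80.
- Enrolment: control 114; intervention 85 + 60 + 86 + 89 = 320; ratio r = 320/114 = 2.81.

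**Step 1: reproduce 200.** With equal arms, the normal approximation gives n per arm = 2 × ((1.960 + 0.842)/0.40)² = 98.1, rounded up to 99, a total of 198. The t-test version gives 100 per arm, a total of 200, with power 0.804. Screen time needs 182 (normal) or 184 (t). The alternatives tried do not return 200: a one-sided test gives 156 at 0.40 SD, a 1:2.81 split about 254, and a 1:4 split 310. Equal arms are therefore inferred, but no other variant tried returns the stated total.

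**Step 2: power of 200 children at the enrolled split.** Control 200 × 114/434 = 52.5; intervention 147.5.
- Standard error in SD units: √(1/52.5 + 1/147.5) = 0.161.
- At 0.40 SD: 0.40/0.161 = 2.49, and Φ(2.49 − 1.96) = 0.702. Noncentral t gives 0.698.
- At 0.417 SD: 0.737 by the normal approximation and 0.733 by noncentral t.

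Put another way, 200 children in this split carry the information of 4 × 52.5 × 147.5/200 ≈ 155 children in equal arms.

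**Step 3: total needed at the enrolled split, 0.40 SD.** n control = (1 + 114/320) × ((1.960 + 0.842)/0.40)² = 66.5. n intervention = 2.81 × 66.5 ≈ 186.8. The total is 253.3 by the normal approximation. By noncentral t, 67 v 187 gives 0.799, and 67 v 188 (255 children) gives 0.80 to two decimals. Screen time needs about 234.

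**Step 4: context.** All 434 enrolled children (114 v 320) give 0.955 at 0.40 SD on the same child-level assumptions.

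The number in grades 3 and 4 is not given. If, as an assumption, it is two-thirds of enrolment in each arm (76 v 213, total 289), power is about 0.85 with no loss, 0.81 with 10% loss, 0.76 with 20% and 0.71 with 30%. It falls below 0.80 once loss passes about 12% (254/289 = 0.88). At 30% loss about 202 children remain, which is above the stated minimum although power is about 0.71. The loss rates are illustrative and do not come from the document.

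**Step 5: what these figures leave out.** Every figure above treats children as independent. As an illustration with an assumed intraclass correlation ρ, take one control school of 67 and 187 children in four intervention schools of equal size, with the school variance treated as known. The variance of the difference in SD units is ρ + (1 − ρ)/67 + ρ/4 + (1 − ρ)/187.
- ρ = 0.01: variance 0.0326, standard error 0.180, power about 0.60.
- ρ = 0.02: variance 0.0449, standard error 0.212, power about 0.47.

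**The case against.** The strongest reply is that the error has little practical effect. Enrolment was complete at 434, far above both 200 and 255, and child-level power with all of them is about 0.955. Even an assumed grade 3 and 4 cohort of 289 starts at about 0.85. This stands. A reader might infer from the 0.70 that the trial as enrolled is underpowered, but the document's figures do not show that before clustering is considered.

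A reader might also infer that following only grades 3 and 4, or loss over two years, helps to produce the 0.70. Neither does. The 0.70 comes from the unequal split alone; grade restriction and loss affect only how many children remain to be compared with the threshold. Nor does the article set 200 against the 434 enrolled, so that comparison should not be attributed to it. The lack of a stated loss allowance is not counted as an error, because a condensed article may leave it to the full protocol.

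It is also fair to object that a corrected 67 and 188 could mislead in turn, because whole schools were assigned and there is one control school. This stands too and limits what the corrected figure can be called. It does not rescue 200, since ignoring clustering makes the figures for 200 optimistic as well.

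Finally, equal arms are nowhere stated. That is so, but under the section's own inputs 200 children at the enrolled split miss 0.80 for all three outcomes, however the figure was obtained.

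**Conclusion.** The concern holds in a limited form. The stated minimum does not deliver the stated power under the study's own allocation: about 0.70 rather than 0.80 for steps and for fruit and vegetables, and about 0.73 for screen time. The child-level requirement at 1:2.8 is about 255, so 200 falls short by about 55 children, or 22% (55/255).

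This rests on a two-sided alpha of 0.05, the three standardised differences as given, the enrolled ratio of 114 to 320, and independence between children. It shows that the stated threshold is too low. It does not show that the enrolled sample is too small on child-level assumptions, and power for the followed cohort cannot be fixed from the article because counts by grade are not given.

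**What to change.** In Setting And Participants, replace the single total of 200 with a minimum for the actual allocation: about 255 children, roughly 67 control and 188 intervention, for the two 0.40 SD outcomes. Say in the same sentence that this is a child-level lower bound which takes no account of clustering by school with a single control school, so meeting it does not by itself establish power 0.80.

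Apply it to the third and fourth graders followed to Spring 2011, not to the 434 enrolled in grades 3 to 5. Report the power for the number actually retained in each arm.

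The cost is restating one figure and adding one line of power results. No extra enrolment and no change to data collection is involved.
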